### The content of the educational modules

3.4

The aim of the modules is to provide the user all relevant information and help them to find a way to commit to the decision they have made and link the change to the user's broader goals and values, with a lack of coercion or direct persuasion from the application, as suggested by Resnicow and McMaster (2012).

The goal of *Module 1—consequences of excessive alcohol consumption and goal setting*—is to urge the user to evaluate the positive and negative consequences of his or her alcohol consumption present and in the future, to present the positive aspects of controlled drinking or abstinence through general descriptions and personal experiences and to set goals regarding alcohol consumption. There are two goal types, either aiming to reduce consumption or total abstinence for a period of time specified by the user. At the end of every module, users have the option to modify their goals.

*Module 2—facilitate action planning and problem‐solving*—is started with personalized feedback reflecting the positive consequences of alcohol perceived by the user and alternatives for replacing them. It is followed by an introduction of the monetary consequences of cutting back derived from the baseline consumption and the goals set in Module 1. After that, the WOOP technique is presented as a tool for action planning. The WOOP technique is an imaginary exercise that increases goal commitment and behavioral change through performing four sequential steps; (1) identifying a meaningful goal (wish); (2) identifying and imagining the best outcome of accomplishing this goal (outcome); (3) identifying and imagining the critical inner obstacle to accomplishing that goal (obstacle); and (4) forming an “if‐then” plan to overcome that obstacle (Saddawi‐Konefka et al., 2017). Also, tips/techniques are presented in three domains; lifestyle changes, techniques for reducing alcohol consumption, and techniques in case of cravings.

*Module 3—identify contextual factors and self‐control practices*—is designed to help users identify risky contextual (where, when, whom) factors, with the option to set specific goals regarding conscious avoidance of risky situations. Marlatt and Donovan (2005) highlight the importance of geographical areas represent a high‐risk situation for relapse, and encourage people to avoid them as much as possible. Module 3 ends with self‐control practices with personal experiences of former heavy drinkers.

*Module 4—refusal skills training*—consists of communication techniques targeting successful refuse of alcoholic drinks and interactive situations for practice. This module helps users to recognize social pressure to drink, and prepare them with lined up strategies to refuse drinks in a confident, yet appropriate way.

*Module 5—relapse management*—covers the exploration of warning signs of relapse, action plans, and general information. The aim of this module is to inform users that temporary relapses might happen, which should not reduce their motivation to achieve their goals. Presenting personal experiences of former hazardous drinkers, users are encouraged to view their consumption goals as a long‐term process, with the possibility to learn from it.

At the final stage of application development, a small group of users (*n* = 8) were involved in app testing. Based on their feedback regarding ease of use, language‐wording, and bugs, the application was modified.

### Control application

3.5

The control application has the same core functions as Yoozan, without the educational modules. With the exception of WHO alcohol consumption guidelines, core functions do not contain explicit information on alcohol use. Thus, the rationale behind applying a control application was to investigate the effectiveness of the core functions in reducing alcohol consumption, without providing information on alcohol‐related topics.

### Wait‐list control group

3.6

7‐day Timeline Followback and AUDIT are assessed, and personalized feedback is given for participants willing to participate in the study. Participants in the wait‐list control group receive access to Yoozan 180 days later.

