To investigate this question, a new smartphone alcohol intervention application was developed—Yoozan—with built‐in timers recording usage times of the different functions separately for every user. A randomized controlled trial will be conducted, where participants will use Yoozan or a control application (with restricted functionality, described in Methods) for 30 days, or will be allocated to a wait‐list control group. By analyzing usage times and the efficacy of the application in reducing the amount of alcohol consumed, the primary aim of the study is to evaluate the relationship between user engagement and intervention efficacy. The secondary aim of the study is to investigate the efficacy of the application functions by investigating the relationship between usage times of the application functions and intervention efficacy. The tertiary aim of the study is to investigate the efficacy of the intervention application compared to an active control application and to a wait‐list control group.

We hypothesize that there will be a positive correlation between engagement (reflected in usage time) and between the extent of reduction in alcohol consumption. We also hypothesize that Yoozan users will consume less alcohol at post‐intervention and 30, 60, 90, 120, 150, and 180 days follow‐up, compared to the participants in the control conditions.

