### Study design

2.1

The aforementioned aims will be achieved in a randomized controlled trial with three parallel arms. Two smartphone application‐based interventions will be compared: a new intervention for reducing harmful drinking (Yoozan) and a control application (Yoozan without educational modules). Assessments will be completed at baseline, post‐assessment (30 days from registration), and follow‐ups at 60, 90, 120, 150, and 180 days (see Figure 1). The study was approved by the Hungarian Ethics Committee (2019/293). Consent is obtained electronically from all participants. The study is conducted in accordance with the Declaration of Helsinki.

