### Recruitment of study participants and trial flow

2.2

Recruitment took place from December 2019 and is currently ongoing. Participants are recruited through promotion articles published on Hungarian Internet portals. In the articles, Yoozan is introduced with a call to participate in testing in case the reader wants to change his/her drinking habits. All interested participants are directed to the webpage of the study, from where the application can be downloaded. Based on a block randomization method, an equal number of participants download either Yoozan, the control application, or allocated to the wait‐list control group. After installing the application, participants are asked to read the participant information sheet and provide informed consent and a valid email address for which usability questionnaire and follow‐ups will be sent (see Figure 1).

Participants allocated to the wait‐list group are informed that 6 months later, the application will be sent to their email addresses and are encouraged to fill a few tests (7‐day Timeline Followback, Alcohol Use Disorders Identification Test [AUDIT]) with instant feedback.

Study inclusion criteria are informed consent via the Web form to ensure knowledge of procedures and the declaration of consent; participant age ≥18 years, to ensure a minimal age of participation; ownership of an Android‐operating smartphone and at least weekly Internet access, to ensure program access; a screening AUDIT score ≥8 out of 40, to include adults with potentially hazardous or harmful alcohol consumption; and an indication of an attempt to reduce alcohol consumption (screening motivation score ≥2 out of 5), to ensure a minimal willingness to change. Exclusion criterion is participation in other treatments for the reduction of alcohol consumption, to avoid confounding treatment effects.

The study targets Hungarian speaking users; thus, the language of the intervention is Hungarian. If the intervention is effective, translation to English and upload to App Store and Google Play is planned.

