### Measures

2.4

At baseline weekly alcohol consumption, AUDIT score, motivation to change drinking habits, and sociodemographic data (age and gender) are assessed. Weekly alcohol consumption is assessed by the 7‐day Timeline Followback (e.g., see Sobell & Sobell, 1992) by users entering the consumption for each day of the previous week from a predefined list of drinks. It allows defining consumption measures that hopefully contribute better comparability between studies (Shorter et al., 2019), such as the frequency of drinking and heavy drinking (on a weekly level) and the summed consumption in standardized units. The AUDIT is a validated 10‐item screening tool developed by the World Health Organization (WHO) to assess alcohol consumption, drinking behaviors, and alcohol‐related problems. It is particularly designed for health care practitioners, but with suitable instructions, it can be self‐administered (Babor, Higgins‐Biddle, Saunders, & Monteiro, 2001). Motivation to change drinking habits is measured with the question “How important is it for you to change your drinking habits?” with five options to answer (1: not important, 5: very important).

The follow‐up questionnaires consist of the 7‐day Timeline Followback and application usability test. Subjective rating of application functions is measured at the first (30 days) follow‐up, with questions regarding the perceived effectiveness of each function helping to reach alcohol‐related goals, with five options to answer (1: very poor, 5: very helpful).

Besides the self‐administered tests, usage times of the application are recorded, and the following variables are formed: total usage, frequency (the number of usage sessions), and usage time of functions.

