### Registration and feedback

3.2

The aim of the registration process is to collect baseline measures (weekly alcohol consumption, AUDIT, and motivation to change, see Table 2) and to provide feedback on the alcohol use of the participants.

**TABLE 2 mpr1848-tbl-0002:** Overview of the measurements

Measures	Baseline (t0)	Day 30 (t1)	180 days follow‐up (t2, t3, … t6)
Demographic (age and gender)	X	‐	‐
Demographic (level of education and place of residence)	‐	X	‐
7‐day Timeline Followback (Sobell & Sobell, 1992)	X	X	X
AUDIT (Babor et al., 2001). World Health Organization	X	‐	‐
Motivation to change	X	‐	‐
Usability ratings of the application	‐	X^a^	‐

^a^
Excluded in wait‐list control group.

Abbreviation: AUDIT, Alcohol Use Disorders Identification Test.

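### Wait-list access to Yoozan falls on the same nominal day as the last follow-up and is not tied to its completion, so late day-180 answers can cover days with access

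*Protocol article*

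**What the plan says.** **Access.** Section 3.6 (Wait-list control group) states that those in the "control group receive access to Yoozan 180 days later". Section 2.2 (Recruitment) tells wait-list participants that "6 months later, the application will be sent to their email addresses". Both are calendar rules. Neither mentions return of the last questionnaire, and section 3.6 does not name the day from which it counts; I take it to be registration.

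**Assessments.** Section 2.1 (Study design) sets a post-assessment "30 days from registration), and follow‐ups at 60, 90, 120, 150, and 180 days". Table 2 agrees: day 30 is t1, and the remaining points are headed "180 days follow‐up (t2, t3, … t6", which is five more. That makes six post-baseline points, ending at day 180. The hypothesis at the end of the Introduction is worded differently, as "post‐intervention and 30, 60, 90, 120, 150, and 180 days follow‐up", which read literally is seven points.

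**Outcome.** Section 2.4 (Measures) assesses weekly consumption with the 7-day Timeline Followback, "by users entering the consumption for each day of the previous week". The follow-up questionnaires use the same instrument.

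**The concern.** The wait-list is the trial's only group without an app, and day 180 is its last point of comparison, so this contrast carries the evidence on six-month persistence against no app. The hypothesis claims a difference at that point. The outcome looks back over a week and access starts on the day the questionnaire falls due. A wait-list participant who answers some days late may therefore describe days on which Yoozan was already available. If Yoozan reduces drinking, such answers lower the wait-list mean and shrink the difference. The limitations in the Discussion cover missing follow-up data but not this overlap. In a remote study that expects 27% of participants to respond even at the first follow-up, it would be unsafe to assume that every returned form comes back on its due day.

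**Working it through.** **1. Overlap of the recall week with access**

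Inputs: questionnaire due on day D = 180 (section 2.1, Table 2); access on day A = 180 (section 3.6, counted from registration by assumption); recall of seven days (section 2.4). A form completed on day D + k covers days D + k − 7 to D + k − 1. The number of those days on or after A is min(k,7) when D = A.

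| Delay k (days) | Days covered | Days on or after access | Share |
|---|---|---|---|
| 0 | 173–179 | 0 of 7 | 0% |
| 1 | 174–180 | 1 of 7 | 14% |
| 3 | 176–182 | 3 of 7 | 43% |
| 7 | 180–186 | 7 of 7 | 100% |
| 14 | 187–193 | 7 of 7 | 100% |

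The shared day alone does no harm; the overlap needs a late answer. The shares are an upper limit, because they count days with access, not days of use or of effect.

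**2. If access follows section 2.2 instead**

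Six calendar months from the first of each month, December 2019 to July 2020, come to 182–184 days. The overlap then begins 2–4 days later than in the table, but it still occurs for later answers.

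**3. Time points**

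| Place | Post-baseline points | Last point |
|---|---|---|
| Abstract, Methods | 30, 60, 90, 120, 150, 180 | day 180 |
| Section 2.1 | 30 from registration, then 60 to 180 | day 180 |
| Section 2.4 | day 30 called the first follow-up | – |
| Table 2 | t1 (day 30), t2 to t6 | sixth point |
| Introduction, hypothesis | post-intervention, then 30 to 180 | not stated |

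Four places fit six points ending at day 180. The Introduction most naturally names the day-30 point twice.

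**4. What dilution could cost (illustration only)**

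The article gives no figure for late answers, so this step rests on assumption. Its planning values are d = 0.20, 80% power and two-sided alpha 0.05, with 394 per group. An exact t-test gives 393.4, which rounds up to 394. The expected number of responders per group at the first follow-up is 4356 × 0.27 / 3 = 392. Suppose that a share f of wait-list answers at day 180 carries the full effect. The expected difference becomes 0.20 × (1 − f), and power is approximately Φ(0.20 × (1 − f) × √(392/2) − 1.96).

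| f | Expected d | Power |
|---|---|---|
| 0 | 0.20 | 80% |
| 10% | 0.18 | 71% |
| 25% | 0.15 | 56% |
| 50% | 0.10 | 29% |

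The table assumes that day-180 response matches the first follow-up and that every affected answer carries the whole effect. It shows how power would respond, not what is expected.

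**The case against.** The strongest reply is that the article is silent on the order of the two messages, on a response window and on any sequencing rule, and that such logistics belong in a full protocol that is not shown. That stands as a limit: a sequencing rule may exist. What remains is that both places describing access give a calendar trigger, on or within a few days of the last assessment.

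A reader might infer that the link goes out together with the last questionnaire, whether or not it has been returned, or that registration at crossover repeats the baseline tests and feedback. The article says neither. Table 1 gives registration to all three groups at the start, and nothing describes what happens at crossover.

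A reader might also take the Introduction's wording to mean follow-up counted from the end of the 30-day intervention. The last point would then be 30 + 180 = day 210, after the whole wait-list has access. The Abstract, sections 2.1 and 2.4, and Table 2 all speak against this. It is a wording slip, not a schedule under which every final wait-list answer is contaminated.

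It is also fair to say that the overlap affects the outcome only if late responders install the app promptly and it acts quickly. The bias, if the app works, would hide a benefit and not create one.

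**Conclusion.** The point holds in a limited form. Access and last assessment share nominal day 180, and the article does not tie one to the other. Wait-list forms answered on time are clean; a form completed k days after access has up to min(k,7)/7 of its recall week after access. If Yoozan works, the bias in the day-180 Yoozan versus wait-list difference is towards zero. Its size cannot be given, because neither the share of late answers nor uptake after access is stated.

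On the day-180 schedule the exposure is one of six time points, in the wait-list comparison under the tertiary aim. Days 30 to 150, the Yoozan versus control-application comparison and the engagement analyses are not affected. Separately, the two access times and the Introduction's list of time points need to be reconciled with the rest of the article. The conclusion assumes that section 3.6 counts from registration and that no unseen document already makes access wait for the last assessment.

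**What to change.** 1. Make the wait-list link follow the last assessment. Either send it on receipt of that questionnaire and, for non-responders, when a stated response window closes, or send it to everyone at window close. The second option avoids giving only the wait-list an incentive to respond.
2. Reconcile the access time in section 2.2 with that in section 3.6, and name the day from which it counts.
3. Align the hypothesis in the Introduction with the six points in section 2.1 and Table 2, days 30 to 180 from registration.
4. For links already sent, log the send date and add a day-180 sensitivity analysis that applies the same completion window in all three arms. Excluding late wait-list forms alone would select on response behaviour in one randomised arm and could itself bias the comparison.

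The cost is a changed email trigger, a few corrected sentences and one sensitivity analysis. Wait-list participants would receive the app later by at most the length of the response window. As recruitment was still under way, the change could still reach later participants, who would need to be told an access time that matches it.

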## RESULTS

4

The composition of our sample will be demonstrated via descriptive statistics of participants' age, gender, and baseline 7‐day Timeline Followback, AUDIT measures, and motivation to change scores. Random imbalances between the intervention and control groups will be examined using chi‐squared tests. To evaluate the efficacy of the intervention, a repeated measure one‐way between‐groups analysis of covariance (ANCOVA) will be conducted. The analysis model will be built with group allocation as the independent variable, change in alcohol consumption as the dependent variables (the difference between baseline and follow‐ups 7‐day Timeline Followback in consumed alcohol units, binge drinking occasions, and drinking frequency), and age, sex, and motivation to change as covariates. Prior to the analysis, we will make sure that the specific assumptions for normality and homogeneity of variance for the one‐way ANCOVA will be met. In situations where data is missing—for example, with participants who are lost to the 6‐month follow‐up—the mixed model approach will be used to estimate missing values.

Multilevel modeling will be used to estimate the relationship between change in alcohol consumption (consumed alcohol units, binge drinking, and drinking frequency), application usage (total usage time, usage frequency, and usage time of functions) and application usability ratings in the educational and control application groups.

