### Sample size calculation

2.3

Based on previous studies, realistic anticipation is a Cohen *d* of 0.20 for the effect size differences between the two study arms. To demonstrate standardized effect sizes, Cohens *d* of 0.20 with power (1−β) of 80% and an alpha of 0.05 in a two‐sided test performed with G*Power software (Faul, Erdfelder, Buchner, & Lang, 2009) 394 individuals would need to be included in each group. Based on the attrition rate of a self‐directed treatment‐seeker sample of Crane et al. (2018), we expect that 27% of study participants will respond to the first follow‐up, increasing the initial sample required by 3180; thus, we aim to recruit a total of 4356 participants.

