The following limitations of the protocol must be considered: (1) all measurements except behavioral data will be self‐reported that may be prone to biases (e.g., social desirability bias), (2) possible unequal group sizes leading to reduced statistical power due to the randomization process occurring before assessment for eligibility, (3) potentially there will be missing follow‐up data of the dropped outs, and (4) the application only available on Android operating smartphones.

Although mobile phones offer the potential to reduce the harms of hazardous drinking (Crane et al., 2015), up to date there have been relatively few studies conducted that evaluate the efficacy of evidence‐based smartphone applications aiming to reduce alcohol consumption (e.g., Crane et al., 2018; Gonzalez & Dulin, 2015; Zhang et al., 2016). By applying a randomized controlled trial, the results of the present study will be comparable with previous studies and will be informative about the overall efficacy of alcohol intervention applications. By investigating the behavioral correlates of the application, we hope that a more complex understanding of application efficacy will be achieved, making more focused intervention development possible in the future.

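### The efficacy model analyses change from baseline but omits baseline consumption as a covariate, which costs precision and over-corrects chance baseline imbalance

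*Protocol article*

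**What the plan says.** Section 4 (Results) of the protocol article sets out the efficacy analysis as a repeated-measures ANCOVA. Group is the independent variable. The outcome is "change in alcohol consumption as the dependent variables (the difference between baseline and" follow-up on the 7-day Timeline Followback, for consumed units, binge occasions and drinking frequency. The model is completed by "and age, sex, and motivation to change as covariates". The list stops there, and no other section adds baseline consumption.

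The baseline value is available. Section 2.4 (Measures) opens with "At baseline weekly alcohol consumption, AUDIT score, motivation to change drinking habits", Table 2 marks the Timeline Followback at t0, and section 3.6 confirms that it is also assessed in the wait-list group.

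On imbalance, section 4 says "Random imbalances between the intervention and control groups will be examined using" chi-squared tests, and states no adjustment for baseline drinking.

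Section 2.3 rests the sample size on this statement: "realistic anticipation is a Cohen *d* of 0.20". With 80% power and a two-sided alpha of 0.05, it concludes that "394 individuals would need to be included in each group". It does not say which SD the effect is scaled by.

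**The concern.** Baseline drinking is likely to be the strongest available predictor of later drinking. Subtracting it is not the same as adjusting for it. A change score gives baseline a coefficient of exactly 1. With equal SDs the efficient coefficient is rho, the correlation between baseline and follow-up. For a single self-reported week, rho can be well below 1.

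Two things follow. The outcome has more residual variance than it needs, so the comparison between arms is less precise than the collected data allow. And if the arms differ at baseline by chance, regression to the mean makes the heavier-drinking arm appear to improve more. Age, sex and motivation remove only the part of this that they predict.

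The covariates are named in the text, so this is a stated modelling choice and not a detail left to an analysis plan.

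**Working it through.** **Inputs.** From section 2.3: d = 0.20, power 80%, two-sided alpha 0.05, 394 per group. From section 4: change as outcome, and the covariates age, sex and motivation. Assumed, because the article does not give it: rho between 0.3 and 0.8. Also assumed: equal SDs at baseline and follow-up, and little prediction of baseline drinking by the listed covariates.

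**The plan's own figure.** A two-sample t-test with d = 0.20, 80% power and two-sided alpha 0.05 needs 393.4 per group, rounded up to 394. The stated figure reproduces. (The stated total implies 4356 − 3180 = 1176 = 3 × 392 analysed. Using 392 changes the powers below by at most one percentage point.)

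**Residual variance, one follow-up, in units of SD².**
- Change score: 2(1 − rho)
- Baseline as covariate: 1 − rho²
- Ratio, adjusted to change: (1 + rho)/2

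The ratio is 0.65 at rho 0.3, 0.75 at 0.5, 0.85 at 0.7 and 0.90 at 0.8. Its inverse shows that the change score needs 54%, 33%, 18% and 11% more participants for the same power.

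**Power at 394 per group.** The scale of d is not stated, so both readings are shown. The t-test uses effect size 0.20 divided by the square root of the relevant variance.

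| rho | d on change-score SD: change / adjusted | d on raw consumption SD: change / adjusted |
|---|---|---|
| 0.3 | 80% / 94% | 66% / 84% |
| 0.5 | 80% / 90% | 80% / 90% |
| 0.7 | 80% / 86% | 95% / 98% |
| 0.8 | 80% / 84% | 99% / >99% |

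**Several follow-ups.** The plan is a repeated-measures analysis, so the single-visit figures are not the whole picture. Suppose k visits are averaged, with a constant effect, the same rho between all visits, and everyone analysed at every visit. The mean follow-up has variance m = (1 + (k − 1)rho)/k. The change score then has variance 1 + m − 2rho and the adjusted model m − rho². The difference between them is (1 − rho)² for any k. At rho 0.3, d on the raw SD and 392 per group:
- k = 1: variances 1.40 and 0.91, power 66% and 83%
- k = 3: variances 0.933 and 0.443, power 82.5% and 99%
- k = 6: variances 0.817 and 0.327, power 87% and over 99%

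Averaging lifts the change score above 80%. By six visits the gap has narrowed from about 18 to 13 percentage points of power. Adjustment stays ahead, and its relative variance advantage does not shrink.

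**Chance imbalance.** If one arm starts 0.10 SD higher and there is no treatment effect, the change-score difference (follow-up minus baseline) is −(1 − rho) × 0.10 SD. That is −0.07 SD at rho 0.3, −0.05 at 0.5 and −0.02 at 0.8, against a target of 0.20 SD. The 0.10 SD is illustrative. With 394 per arm, the standard error of a baseline difference is √(2/394) = 0.071 SD, so 0.10 SD is 1.40 standard errors, and a gap at least that large between two given arms arises by chance about 16% of the time. A simulation fixing this imbalance (rho 0.5, 394 per group, no effect, 4,000 runs) gave a mean estimate of −0.048 SD and 7.7% rejection for the change score. With baseline adjustment it gave 0.002 SD and 5.3%.

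**The case against.** The strongest reply is that change from baseline is a valid outcome in a randomised trial. It uses the baseline by subtracting it, and its estimate is unbiased on average over randomisations. That stands. A reader might infer that baseline imbalance is left wholly untouched. It is not: it is over-corrected, and the bias is conditional on an imbalance that has occurred.

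A reader might also infer that the trial is underpowered. The article does not support that. A shortfall below 80% requires d = 0.20 to be on the raw consumption SD, rho to be below 0.5, and the test to rest on essentially one follow-up. The article states none of these. If d refers to the planned change outcome, 394 per group gives the stated 80% and adjustment is a bonus. The averaging calculation in turn assumes complete visits, while section 2.3 expects only 27% to respond at the first follow-up. If each visit is tested separately, the single-visit figures apply.

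A third tempting inference comes from section 5 (Discussion), which mentions the "randomization process occurring before assessment for eligibility". The article links this to unequal group sizes and reduced power, not to different baseline drinking. Nor would adjustment reliably remove a systematic difference. For a stable true difference of 0.10 SD measured with reliability 0.5, the adjusted estimate is off by 0.10 − 0.5 × 0.10 = 0.05 SD, while the change score is not biased. The case for adjustment therefore rests on precision and chance imbalance only.

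Finally, the comparison between arms is the tertiary aim (section 1). This lowers the priority, although the comparison is also a stated hypothesis and the one for which the sample size was calculated.

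**Conclusion.** The point holds as a matter of efficiency and of conditional bias. The stated model omits a covariate that is collected on everyone and that reduces the residual variance for any rho below 1. For one follow-up with equal SDs, the reduction is to between 0.65 and 0.90 of the change-score variance over an assumed rho of 0.3 to 0.8. The gain in power is large at low rho. At rho 0.7 or above it is modest: three points at most if d is on the raw SD, four to six if it is on the change-score SD. The change-score analysis is valid on average, so this should be fixed but does not undermine the trial.

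**What to change.** In section 4, add the baseline value of the same outcome (units, binge occasions or drinking days, as the case may be) as a covariate beside age, sex and motivation to change. Either change or the follow-up value can be the outcome: once baseline is in the model, the group estimate is identical. It would also help to say in section 2.3 which SD d = 0.20 refers to.

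The cost is one line of wording for the model and one clause for the effect size. No new data, participants or assessments are needed. The change should be made before the efficacy analysis is run.

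### Efficacy analysis: a change-score model that omits baseline consumption and AUDIT cannot estimate missing values when 73% are expected to miss the first follow-up

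*Protocol article*

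**What the plan says.** All references are to the protocol article.

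- **Sample size calculation (2.3).** The target is a Cohen d "of 0.20 for the effect size differences between the two study arms", with power "of 80% and an alpha of 0.05", so that "394 individuals would need to be included in each group". On attrition: "we expect that 27% of study participants will respond to the first" follow-up. Recruitment is raised by 3180 to 4356.
- **Study design (2.1) and Table 2.** The 7-day Timeline Followback is taken at baseline and at days 30, 60, 90, 120, 150 and 180. AUDIT is taken at baseline, and Table 1 places the baseline tests in all three groups.
- **Results (4).** Efficacy is to be tested by a repeated-measures ANCOVA. The dependent variable is the difference between baseline and follow-up in units, binge occasions and drinking frequency. The covariates are age, sex and motivation. For missing data, with loss to the 6-month follow-up as the example, "the mixed model approach will be used to estimate missing values".
- **Discussion (5), limitations.** "potentially there will be missing follow"-up data from those who drop out.

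**The concern.** The sample size section treats non-response as the expected state of nearly three participants in four at day 30. The analysis section treats it as an exception that a mixed model will repair by estimating what is absent. A mixed model does not do that. It estimates group and time effects from the outcomes that were observed. Its answer applies to all randomised participants only if response, given the variables in the model and the follow-ups already observed, does not depend on the unseen outcomes.

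Two choices in the article make that assumption harder to meet. First, the outcome is a change score, so a person with a baseline but no follow-up has no record at all. Second, the two baseline measures most directly tied to later drinking, baseline consumption and AUDIT, are collected but left out of the covariates. If heavier drinkers are more, or less, likely to answer in one arm than in another, the contrast between arms is biased although the data to correct it are in hand. Precision is also given away. The target effect is small, so a modest bias matters.

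**Working it through.** **1. Reproduce the plan's figures.** Inputs from section 2.3: d = 0.20, two-sided alpha 0.05, power 80%, 27% response.
- The two-sample t-test gives 393.4, rounded up to 394 per group, as stated.
- Total: 3 x 394 / 0.27 = 4378. The stated 4356 equals 3 x 392 / 0.27. The difference is 0.5%, and power at 392 per group is 79.9%, so it is immaterial.
- Expected without a day-30 outcome: 0.73 x 4356 = 3180, or about 1060 of 1452 per arm. About 392 per arm respond.

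**2. What a mixed model on change scores does with non-responders.** A simulated trial had 4356 randomised and 27% with any follow-up. A mixed model was fitted with group, time, age, sex and motivation.
- Full file of 4356 people: estimate -0.1770, SE 0.0578, 6061 records used.
- The 1206 responders alone: estimate -0.1770, SE 0.0578, 6061 records used.

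The results are identical. People with no follow-up add nothing and nothing is estimated for them.

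**3. Cost of leaving out baseline consumption: precision.** Take SD 1 at baseline and follow-up, with correlation r between them. The documents do not give r.
- Variance of the change score: 2(1 - r). Variance after baseline adjustment: 1 - r². Ratio: (1 + r)/2.
- r = 0.4, 0.6, 0.8 gives 0.70, 0.80, 0.90, so adjustment lowers the variance by 30%, 20% or 10% at a single follow-up.

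**4. Cost of leaving out baseline consumption: bias.** Assume no true effect, 27% response in each arm, and response that rises with baseline consumption in one arm only, with log-odds of 0.25 per SD.
- Responders in that arm then start about 0.18 SD above the arm's mean.
- Bias in the change-score contrast is about (1 - r) x 0.18. At r = 0.6 this is 0.4 x 0.18 = 0.07 SD.
- For r = 0.4 it is 0.6 x 0.18 = 0.11 SD, and for r = 0.8 it is 0.2 x 0.18 = 0.04 SD.
- In simulation, adding baseline consumption as a covariate brought the bias to 0.005 SD or less in absolute value in each case.

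**5. What adjustment does not cure.** Suppose response depends on the follow-up outcome itself.
- The responder mean in an arm differs from the mean of everyone in that arm by (1 - 0.27) x gap, where gap is the responder minus non-responder difference.
- Assume a gap of 0.2 SD in one arm and none in the other: bias = 0.73 x 0.2 = 0.146 SD, against a target of 0.20.
- With the same selection in both arms (log-odds 0.25 per SD), the simulated difference is 0.00 SD and the false-positive rate stays at 5%.
- With one-arm selection on the part of follow-up that baseline does not explain (log-odds 0.25 per SD), bias is 0.144 SD for the change score and 0.147 SD with baseline adjustment. Adjustment does not touch this component.

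**The case against.** Several objections carry weight.

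- **Attrition is not concealed.** Section 2.3 quantifies it and recruits for it. The word chosen in the limitations is a matter of tone. This stands, but recruiting more people restores precision and does nothing for selection.
- **The 73% concerns the first follow-up only.** Five more are scheduled, and anyone who answers one of them enters a mixed model. This stands: 3180 is an upper figure, and the share who never respond is not given. A reader might infer that 3180 people are certain to fall out of the efficacy estimate; the article does not support that.
- **The plan does not rest on complete cases.** A reader might infer that only people with all six follow-ups would be analysed. The article turns to a mixed model when data are missing, and that model keeps partial responders.
- **Bias is a risk, not a finding.** Outcome-dependent response in one arm is an assumption. The two app arms share their core functions, so different selection is less obvious between them than against the wait-list. A reader might infer that the result will be biased, but equal selection leaves the contrast unharmed.
- **Sensitivity analyses and distributional fallbacks belong in an SAP.** A separate SAP may contain them. Their absence from an article is not the fault here, nor is the intention that "we will make sure that the specific assumptions for normality and homogeneity of variance" will be met.
- **Efficacy against the controls is the tertiary aim.** True, but the sample size is built on a difference between arms.

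A reader might also infer that setting non-responders to baseline would leave the trial with little power. That does not follow: those participants would have a change of exactly zero, so the spread shrinks along with the mean difference.

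**Conclusion.** The concern holds for what the article itself fixes: the change-score outcome, the short covariate list, and a mixed model described as a means of estimating missing values while 73% are expected to lack a day-30 outcome. That description is wrong, and leaving out baseline consumption and AUDIT is an avoidable weakness.

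The avoidable part, under selection on baseline in one arm, is about 0.07 SD (0.04 to 0.11 for correlations of 0.8 to 0.4), plus a 10% to 30% loss in variance terms. The part that no such model removes is 0.146 SD if responders and non-responders differ by 0.2 SD in one arm only, and about zero if selection is equal. The correlations, selection strengths and the 0.2 SD gap are assumptions; only the 27%, 4356 and 0.20 come from the plan. The documents do not show that bias will occur.

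**What to change.** 1. Name one longitudinal mixed model on all observed assessments as the efficacy analysis, with group, time, group x time, age, sex, motivation, AUDIT and baseline consumption. Baseline consumption can enter as a covariate, with consumption at each follow-up as the outcome, or as a first repeated measure constrained equal across arms.
2. Replace the statement about estimating missing values with the assumption actually made: missing at random given the model's variables and the observed follow-ups.
3. Report response by arm and wave.
4. Because this model still assumes missing at random, add a sensitivity analysis that does not: a delta shift for non-responders, or non-responders set to their baseline consumption. If the SAP already has one, refer to it.

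The cost is wording and programming. No new data are needed, since baseline consumption and AUDIT are already collected. The downside is that the sensitivity results may be less favourable than the main estimate. The change should be made before outcomes are examined.
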